#### Process evaluation

We will calculate descriptive statistics for the quantitative items of the RE-AIM outcome measures. Thematic content analysis will be performed for the semi-structured interviews on adoption, implementation and maintenance. To understand why the implementation strategies did or did not work, we will construct causal pathway diagrams that map the mechanisms, determinants, and proximal and distal outcomes of each implementation strategy [60].

### Patient and public involvement

Patient and public involvement is embedded throughout the project and documented in the patient involvement matrix (Supplementary 8). We collaborate with the Dutch Child and Care Foundation (*Stichting Kind en Zorg*), which provided advice on the grant proposal, patient information letters, recruitment strategy and qualitative research. They will also support dissemination of the study results to the public. Additionally, a patient panel (two parents and one child with a history of acute abdominal pain) advised on the information letter, decision-making tool and recruitment strategy, and will contribute to the sharing of results.

## Discussion

To our knowledge, this study is the first to evaluate the impact of a diagnostic strategy for appendicitis that combines an externally validated prediction rule and CRP POCT with risk-based management advice in children with acute abdominal pain in primary care. By providing GPs with more guidance in their decision making, the diagnostic strategy could reduce uncertainty. We hypothesise that this will, in turn, help lower referral rates without compromising safety, thereby improving patient outcomes (e.g. quality of life, anxiety, satisfaction) and reducing healthcare costs [61, 62].

To ensure clinical relevance and validity, diagnostic strategies must be developed and tested in the setting where they are intended to be used [63]. This typically follows sequential phases: development, accuracy assessment, evaluation of clinical and cost-effectiveness, and implementation [23–25]. To date, prediction rules for appendicitis have predominantly been developed in secondary care, with few being evaluated for impact in RCTs [19, 64]. However, these rules are not suitable for use in primary care, where children present earlier and with different symptom profiles, laboratory tests (e.g. white blood cell counts) are not readily available at the point of care, and diagnostic decisions focus on referral rather than imaging or surgery [65, 66]. Therefore, our group developed a prediction rule tailored to primary care, which forms the basis of the diagnostic strategy assessed in this trial [20]. The CRP cut-offs used in the diagnostic strategy (10 and 50 mg/L) are based on previous research in primary care [21] and supported by evidence from secondary care, where CRP ≥ 50 mg/L showed the highest specificity of all blood tests (0.87; 95% CI 0.80–0.91) [67]. However, implementation of CRP POCT will also depend on the acceptability and perceived burden of additional blood testing among children and their parents, which will be explored in the qualitative study.

Impact trials of diagnostic prediction rules are rarely conducted in primary care, largely due to their complexity, costs, and duration [22]. Nevertheless, we opted for an RCT to generate the highest possible level of evidence [68]. An additional strength of our study is its pragmatic hybrid type 1 design, which enables simultaneous evaluation of effectiveness and implementation outcomes, supporting direct translation of the study findings into daily practice [69–72]. Further strengths include the use of implementation strategies to optimise adherence, as well as a three-month follow-up period that allows comprehensive assessment of healthcare resource use. We selected referral efficiency as the primary outcome, in line with recommendations by Reilly et al. [22]. Safety was defined as a secondary outcome, as using it as a co-primary outcome would have required an unfeasibly large number of children with appendicitis. Therefore, although the results will provide supportive evidence regarding the safety of the intervention, any observed differences between the arms in this outcome must be interpreted with caution due to the lack of adequate power. There could be some misclassification in diagnosing appendicitis, as there are rare cases of spontaneously resolving appendicitis that might be missed [73]. However, since these cases would not require a referral for surgery, this misclassification will not influence the clinical relevance of our outcome.

Still, our study has some limitations. First, although the cluster design reduces potential contamination between GPs [74, 75], it can introduce selection bias if GPs in the intervention arm include children with different characteristics (e.g. more severe symptoms) than those in the control group [76]. To address this, missed eligible children are identified retrospectively via GP registries, and their characteristics compared with those of included children for both groups, with adjusted analyses conducted if baseline differences are observed. Second, GPs and patients are not blinded, which may lead to bias. However, we consider this bias to be limited, as pragmatic trials assess overall effects on the care pathway rather than isolated intervention effects [27]. Third, children presenting at out-of-hours primary care service are not included because of logistical constraints related to the inclusion of GPs and children at these services, particularly the training of an unfeasibly large number of GPs and the reviewing of medical records at numerous individual practices within the service’s catchment area. This may limit generalizability of findings to out-of-hours settings due to potential differences in urgency and severity of appendicitis.

In summary, this study will evaluate whether a diagnostic strategy for appendicitis in children presenting to their GP with acute abdominal pain can reduce referrals to secondary care without increasing delayed diagnoses, compared to usual care. If our hypothesis is confirmed, the findings may support its adoption in routine practice, ultimately contributing to more efficient care and better outcomes for these children.

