### Recruitment

GP practices from three primary care networks (*Academic General Practitioner Development Network of UMCG*, *Julius General Practitioners Network of University Medical Center Utrecht* and *Extramural Leiden University Medical Center Academic Network*) and from the study team’s network are invited to participate by email. Participating GPs and GP trainees will recruit eligible children during office-hour consultations. Additionally, GP assistants will perform a monthly search of the primary care electronic health records (EHRs) of enlisted children using selected International Classification of Primary Care (ICPC) codes to identify and invite eligible children who have been missed by the GP (Supplementary 1).

Figure 3 outlines the recruitment process of children. During or after the consultation, the GP informs eligible children and/or parents about the study and asks consent to share contact and consultation data with the study team via an electronic case report form (CRF).

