**Fig. 3 Fig3:**
[figure not shown]
Recruitment process including data collection timeline. Anonymised baseline data (age, sex, date of baseline consultation, and randomisation group) will be collected for children who meet the inclusion criteria but do not provide consent to share contact details, or who object to participation after contact

Upon retrieval of the contact and consultation data, the study team sends an email to the parent or child, including a patient information letter and informed consent form (Supplementary 2). Patients provide written consent for participation in the study, which includes completing questionnaires, and provide separate consent for collecting relevant data from the child’s EHR. If there is no response within seven days, the study team follows up by phone to provide further study details and to answer any questions.

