### Randomisation, allocation and blinding

GP practices are randomly allocated to the intervention or control group using computer-generated 1:1 permuted-block randomisation with randomly varying block sizes, with stratification based on practice size (above or below 5000 patients). The randomisation is performed by an independent methodologist ([name], PhD). Blinding of GPs and patients is neither feasible nor appropriate in this pragmatic study [27]. Additionally, blinding of outcome assessors is not possible. However, data analysis will be conducted blinded to group allocation, meaning that the data analysts will be unaware of participant assignment until the analysis is complete. During the annual visits to participating general practices, the research team will verify any GP staffing changes. If a GP transfers from an intervention to a control practice or vice versa, their participation will be discontinued to avoid contamination.

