#### Clinical decision support tool integrated in primary care EHR system

Participating GPs receive an electronic clinical decision support tool integrating the diagnostic strategy into the primary care EHR system. The tool was developed in collaboration with software developers (ExpertDoc and Health Base). It is available in two formats, depending on the practice’s type of EHR system. Both versions were tested and approved by six academic and non-academic GPs from the project team.

For GP practices using Medicom as EHR system, the diagnostic strategy is directly integrated into the EHR. It appears in real time as a pop-up when an ICPC-code for gastrointestinal symptoms (D.xx) is entered for children aged 4 to 18 years, enabling the GP to record the presence of signs and symptoms, and CRP POCT value if needed, and receive tailored recommendations.

For non-Medicom practices, direct integration into the EHR was not feasible. Instead, GPs access the tool via a REDCap (Research Electronic Data Capture) link, either through a desktop application or the NHGDoc Classic button. This button, available in five Dutch EHR systems (CGM, OmniHIS, Promedico ASP, microHIS, Bricks), turns yellow when an ICPC D.xx code has been entered, directing the GP to the REDCap tool.

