### Data collection

GPs will complete a baseline CRF for eligible children during the initial consultation, which contains the inclusion and exclusion criteria, contact details of the parent or child, and questions on whether CRP POCT or referral was performed, and why. For GPs in the intervention group, the diagnostic strategy is also included (Supplementary 6).

Medical record data will be collected for all participating children using a standardized form (Supplementary 7). Parents and/or children will complete electronic questionnaires on secondary outcomes via REDCap. Parents complete questionnaires for children ≤ 7 years. For children aged 8–15 years, both the child and parent complete questionnaires separately. Children ≥ 16 years complete all questionnaires independently, except for the cost questionnaire, which they fill out together with a parent.

Questionnaires are emailed at 30 days and 3 months after baseline. Automated reminders from REDCap are sent after 5 days and 10 days. If questionnaires remain incomplete after 10 days, the study team follows up by phone.

All study-related and participant information is stored securely at the study site on institutional servers of the University of Groningen and the University Medical Center Groningen, accessible only to authorized researchers.

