### Data analysis

#### Clinical effectiveness

We will present descriptive statistics to summarise and compare baseline characteristics of GPs and children between the intervention and control groups. The primary analysis will be on an intention-to-treat basis, i.e. based on the randomised group allocation of the children’s GP practice, regardless of the actual care received. Additionally, a per protocol analysis will be performed, including only children in the intervention group who received the diagnostic strategy and CRP POCT as intended, and children in the control group who did not undergo CRP-testing.

Analyses will be carried out on the individual patient level. Dichotomous outcomes (proportions) will be analysed using logistic mixed-effect regression models with fixed effects for group allocation and practice size, and a random effect for practice to account for clustering of patients within GP practices. Continuous outcomes will be analysed using linear mixed effects regression models with the same approach. When outcomes are measured repeatedly, an additional random effect for patient will be included to account for within-patient correlation, along with fixed effects for time and, if appropriate, its interaction with allocation. If necessary, fixed effects for clinically meaningful differences in baseline characteristics will be included in supplementary analyses. Exploratory analyses will be performed to assess subgroup differences in effectiveness by age and sex through inclusion of the corresponding treatment-by-subgroup interaction terms in the regression models.

Estimates of intervention effects ((adjusted) mean differences or ORs, as appropriate) are presented with 95% confidence intervals (CIs). Adverse health outcomes (e.g. complications in appendicitis cases and non-appendicitis cases, missed other emergency diagnoses) will be summarised descriptively, without further statistical analysis.

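### Unblinded GPs recruit after practices are randomised, so case mix may differ by arm; data on decliners cannot show severity, and covariate adjustment is only supplementary and conditional

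*Protocol article*

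**What the plan says.** All references are to the protocol article.

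- **Randomisation, allocation and blinding:** "GP practices are randomly allocated to the intervention or control group using computer-generated 1:1 permuted-block randomisation", and "Blinding of GPs and patients is neither feasible nor appropriate in this pragmatic study".
- **Recruitment:** "Participating GPs and GP trainees will recruit eligible children during office-hour consultations". Consent to pass data to the study team is sought in the consultation or afterwards. Practice assistants also search the records every month by ICPC code and invite eligible children the GP overlooked. No restriction to one arm is stated.
- **Clinical decision support tool:** in Medicom practices, "It appears in real time as a pop-up when an ICPC-code for gastrointestinal symptoms (D.xx) is entered" for a child aged 4 to 18. Other practices reach the tool by a REDCap link, through either a desktop application or a button that turns yellow after a D.xx code. The section on usual care says that control GPs receive a guideline summary and nothing further.
- **Fig. 3 legend:** for eligible children who refuse to share contact details or who object later, "Anonymised baseline data (age, sex, date of baseline consultation, and randomisation group) will be collected".
- **Data collection:** the baseline case report form (CRF) includes the diagnostic strategy for intervention GPs. No equivalent is described for control GPs.
- **Clinical effectiveness:** the model for binary outcomes contains allocation, practice size and a random practice term. Beyond that, "If necessary, fixed effects for clinically meaningful differences in baseline characteristics will be included in supplementary analyses".
- **Discussion:** selection by GPs is the first limitation named, with more severe symptoms in the intervention arm as the example. The stated answer is to compare missed with included children in both groups, "with adjusted analyses conducted if baseline differences are observed".

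**The concern.** In a cluster trial where the recruiter knows the allocation, randomising practices does not guarantee comparable children. Here the cue to think of the study also differs by arm: a code-triggered prompt exists in some intervention practices and none is described for control practices. Because consent may be sought after the consultation, the referral decision can already be known when a child is enrolled.

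The primary outcome is the proportion not referred among children without appendicitis, and that proportion depends strongly on how suspicious the presentation is. A difference in severity between the enrolled groups would pass straight into the effect estimate. The protocol recognises the risk, so the question is whether its safeguards can detect or correct it.

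**Working it through.** **1. The plan's own figure.** Inputs from Sample size considerations: 88% versus 95%, two-sided 5%, 80% power, cluster size 3, intraclass correlation 0.01.

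- Two proportions, pooled variance, no continuity correction: 248 per arm.
- Design effect: 1 + (3 − 1) × 0.01 = 1.02. Then 248 × 1.02 = 252.96, so 253, which is 85 whole clusters of 3 = 255 per arm, 510 in total. This matches the plan.
- Loss to follow-up: 510 / 0.9 = 566.7, stated as 566.

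The sample size therefore reproduces. The target effect against which any bias should be judged is 7 points.

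**2. What is described about severity, by group of children.**

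| Children | Data described | Can severity be compared between arms? |
|---|---|---|
| Participants, intervention | CRF with rule items; medical records | Not from the CRF |
| Participants, control | CRF without rule items; medical records | Not from the CRF; possibly from records (Supplementary 7, not shown) |
| Missed, found by the search | Invited; compared on characteristics that are not listed | Not stated |
| Decline to share details, or object later | Age, sex, date, arm | No |

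Record extraction is described for participating children and needs a separate consent, so it cannot fill the last row.

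**3. Adjustment.** The primary model is fixed and has no patient-level covariate. Adjusted models are supplementary and depend on what is observed. The trigger is worded differently in Clinical effectiveness and in the Discussion, and neither gives a threshold.

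**4. Illustrative size.** The documents give no case mix, so these inputs are assumptions. Among children without appendicitis, let a share s be mild with 2% referred, and the rest suspicious with a proportion r referred. Efficiency is E(s) = 1 − [0.02s + r(1 − s)].

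- Choose r so that E(0.70) = 0.88: r = (0.12 − 0.70 × 0.02) / 0.30 = 0.353, about 35%.
- E(0.80) = 1 − (0.016 + 0.0707) = 0.913, a shift of +3.3 points.
- E(0.85) = 1 − (0.017 + 0.0530) = 0.930, a shift of +5.0 points.
- In the other direction, E(0.60) = 1 − (0.012 + 0.1413) = 0.847, a shift of −3.3 points.

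Each 10-point change in mix moves efficiency by 0.10 × (0.353 − 0.02) = 3.3 points.

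**5. Consequence for the test.** Again on assumed case mix, with 255 per arm and design effect 1.02.

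- No true effect, with extra mild cases (98% not referred) added to the intervention arm. At 30%: 0.7 × 0.88 + 0.3 × 0.98 = 0.91, a spurious 3.0 points and about a 19% chance of a significant result favouring the strategy (nominal 2.5%). At 10% it is 1.0 point and about 5%; at 50%, 5.0 points and about 48%.
- True effect 88% versus 95%, with extra severe cases (70% not referred) in the intervention arm. At 5%, 10% and 20%, observed efficiency is 93.75%, 92.5% and 90.0%, and power falls from 80% to about 61%, 40% and 11%.

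**The case against.** The strongest defence is the monthly search. It does more than count missed children: it invites them, with no restriction to one arm, and so works directly against GPs overlooking mild cases. This stands, and none of the illustrations above allows for it. The authors also disclose the limitation, and record extraction may supply severity for participants who consent to it.

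Four stronger readings are tempting, and the document does not support them.

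- **That the safeguard looks only at age and sex.** The short list in the Fig. 3 legend concerns children who decline or object. The Discussion's comparison concerns missed children and does not list its characteristics.
- **That the bias must favour the strategy.** The Discussion's own example, more severe children in the intervention arm, would work against it. Both directions are plausible.
- **That the primary result depends on the data through the choice of model.** The primary model is fixed. The conditional trigger affects supplementary analyses only.
- **That every intervention GP is prompted.** The pop-up exists only in Medicom practices, the yellow button only in some others, and no prompt is described for the desktop application. The tool also opens decision support; enrolment still needs the GP to inform the family and ask consent. That only the intervention arm has the tool is itself a firm inference from the sections on usual care and implementation strategies, because the tool section speaks of participating GPs in general.

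A covariate list may sit in an analysis plan that is not shown, so its absence is not the point. The conditional rule is the point, because the article states it.

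**Conclusion.** The concern holds in a limited form. Recruitment by unblinded GPs after allocation, with cues that differ by arm, leaves the primary outcome open to a case-mix difference of unknown size and direction. The monthly search reduces it. What remains is that, among children who decline, nothing described could reveal a severity difference; that the CRF as described gives no severity measure common to both arms; and that patient-level adjustment is left to supplementary analyses triggered by observed imbalance.

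The 3-point and 5-point figures rest wholly on the assumed 2% and 35% referral rates and the assumed shifts in mix. They show that a moderate imbalance could be a material fraction of the 7-point target, not that such an imbalance will occur.

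**What to change.** 1. **Primary model.** Include age and sex unconditionally, in place of the conditional trigger. Both are already collected, and sex is a predictor in the rule. This removes age and sex imbalance and may gain some precision (in a logistic model, mainly as power). It does not remove severity bias, and the text should say so. Cost: a few words, best settled before the analysis.
2. **Index referral for non-participants.** Add referral yes/no to the anonymised data on eligible children who do not take part. Report the index referral proportion among all eligible children by arm as a pre-specified sensitivity check. State its limits: it includes children with appendicitis; it is available only from the date it is added, while enrolment began in March 2025; and it misses referrals at planned reassessment, which Table 3 counts, unless the field is worded to cover them. Cost: an ethics amendment, needed because these children did not consent to sharing consultation data, and a little more work for practices.
3. **Recruitment flow.** Report eligible, missed, invited and included children and the route of entry (GP or record search) by arm, descriptively. Do not estimate effects by route: route arises after randomisation and may itself depend on arm. Cost: minimal.
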